#### EKG-gated calcium scoring during single breath hold will be obtained using 2.5 mm slice thickness.

*Timing Test Bolus*

A test bolus is used to determine scan delay time.

Figure 1 A. Time Bolus Tracking Location; B. Left Main Artery Take Off

[figure not shown]

As illustrated in Figure3, to perform timing bolus, a tracking line is placed at the base of the heart (A), usually 1 cm below carina. On the axial view, this location corresponds to root of aorta near left main artery takeoff (B).

The timing test bolus protocol is described in Table 1.

| Table 1 Test Bolus Protocol | |
| --- | --- |
| Monitor Location | Aorta root near left main take-off (see picture below) |
| Scan type | Axial |
| Rotation time | 0.5 sec |
| Detector Collimator | 5 mm |
| Slice thickness | 5 mm |
| Interval | 0 |
| kV | 120 |
| MA | 80 |
| Pre-scan delay | 5 sec |
| Number of slices | 12-14 with 2 second cycle time |
| IV contrast volume and type | Visipaque 20 mL / 20 mL saline flush if dual barrel injector |
| Injection rate | 5mL/sec |

Once all of the test bolus images are reconstructed, the region of interest (ROI) will be selected and the measurement of contrast attenuation on each slice will be performed.

Figure 4 Example of a Graph Image

The measurement values are used to generate graph images. An example of a graph image is shown in Figure4. In this case, the peak of the curve is at the 7th tic mark on the line graph. Each tic mark represents 2 seconds with the peak of the curve occurring at 14 seconds. Since the initial pre-scan delay (or prep group delay) is 5 seconds, the time it takes for the contrast to reach the peak enhancement at the root of the aorta near left main artery takeoff is 14 + 5 = 19 seconds.

*Contrast administration*

Once appropriate scan parameters have been determined, the power injector will be programmed. The contrast agent will be administered using the injection protocol shown in Table 2

| Table 2 Visipaque Administration for Double-Barrel Power Injectors | | | |
| --- | --- | --- | --- |
| Phase | Product Name | Main Volume (mL) | Injection Rate (mL/Sec) |
| 1^st^ phase contrast | Visipaque 320 mg-I/mL | 70 | 5 |
| 2^nd^ phase mixture | 70% Visipaque and 30% 0.9% sodium chloride solution | 50 | 5 |
| 3^rd^ phase saline | 0.9% sodium chloride | 50 | 5 |

*Scan Parameters*

Scan parameters are set according to manufacturer recommendations/specifications. The typical range of the scan parameters is summarised in Table 3.

| Table 3 Scan Parameters for CT Scanner | |
| --- | --- |
|  | **64 – Slice Technology** |
| Application | Triple Rule out |
| Specific anatomic region | Chest |
| kV | 120 |
| MA | 400 – 800 (patient weight dependent) |
| Scan coverage | Top of lung to bottom of heart |
| Image order | Craniocaudal |
| Rotation time | 0.35 sec |
| Detector Collimator | 64 x 0.625 mm |
| Slice Thickness | 0.625 mm |
| Pitch | 0.2 mm – variable based on HR |
| Feed / Rotation (mm) | 8 –12 mm |
| Reconstruction interval | ≤0.5 mm |
| IV Contrast Volume and Type | 100 mL Visipaque / 70 cc saline flushing |
| Injection Rate | 5 cc/sec |

**CT Image Evaluation/Procedures*:***

Two blinded readers who are qualified by their clinical training will be selected for evaluation of the CT images independently. All blinded reviewers must have no financial conflict. The independent image evaluation will be performed at a central imaging core-lab. Planar, cross sectional non-contrast and contrast CT images are compiled for analysis using GE AW 4.2 or higher workstation.

- Cross sectional, longitudinal, and curved planar CTA images will be reconstructed. Multiplanar images are created and reconstructed into a 3 dimensional rendering using the GE algorithms.
- Non-cardiac causes of acute chest pain will be evaluated and recorded, including pulmonary embolus, aortic dissection, lung parenchyma abnormalities, mediastinal abnormalities, other aortic abnormalities, rib fracture, pleurisy, etc.
- Coronary calcium scoring is calculated by the Agatston method, as well as volumetric and mass measurements.
- A 21 segmental ACC/AHA model of the coronary tree will be used for the coronary evaluation.
- For the coronary evaluation, two independent readers must review at least 10 imaging segment phases of images to determine:
- Overall image quality from single best phase for each of the 15 coronary segments in vessels 1.5 mm in diameter or larger.
- Coronary artery supply dominance and coronary anomalies
- Coronary artery segmental interpretability and vessel size down to 1.5 mm
- Presence or absence of coronary artery stenosis/occlusion
- Presence or absence of coronary plaque and characterizing vessel segment plaque as non-calcified, mixed, and calcified or combinations thereof. Non-calcified is defined as less than 40 HU, mixed is 40-150 HU, calcified is greater than 150 HU. A single lesion will be chosen for HU measured: that lesion showing greatest degree of negative or positive remodeling. Further, the segment extent of involvement will be visually graded as trace plaque (less than 10% of length of the vessel segment involved), mild plaque (10-25%), moderate (25-50%), or severe (50-100%).
- If a coronary stenosis >30% is suspected, CT quantitative coronary angiography analysis (QCA) is performed on the lesion to calculate minimal vessel lumen diameter and luminal area. Percent stenosis is calculated based on the proximal coronary considered non-significantly diseased divided into the minimal diameter and area of the lesion.

**Laboratory Analysis:**

- Patients undergo routine lab evaluation that includes complete blood count, comprehensive metabolic analysis (a.k.a., SMA-12), PT and PTT, troponin I/CPK/CK-MB/myoglobin every 8 hours, and lipid panel.
- Approximately 20 cc of blood will be collected into 2 red top tubes for additional testing. The blood will be analyzed for high sensitivity C-reactive protein, apolipoprotein A and B, d-dimer, hemoglobin A1C, and erythrocyte sedimentation rate.

**Treadmill Stress Testing Analysis:**

When clinically indicated, data from subjects undergoing treadmill stress testing will be assembled. Data points include treadmill duration, METS estimation, ECG ST segment measurements and morphology, and clinical symptoms. Data will be assembled and read independently by by two observers who will record disagreements but attempt to reach consensus. The stress test will be considered positive for ischemia if established criteria are met.

**Radionuclide Stress Testing:**

If a stress test with cardiac imaging is deemed necessary by the patient’s primary care team, a pharmacologic stress test will be administered. Either SPECT or PET will be used. Dipyramidole and adenosine are short acting arterial vasodilators that dilates coronary arteries to shunt blood flow away from a region supplied by a partially blocked coronary artery. To measure baseline myocardial blood flow, 20 mCi of ^99m^Tc- tetrofosmin or 20 mCi of ^13^N-ammonia will be injected IV as a bolus followed by dynamic image acquisition for a total 10 minute scan time. After approximately 30 minutes for radiotracer decay, stress testing with IV dipyramidole or adenosine begins. At approximately 6 minutes, a PET scan is acquired using 20 mCi of ^13^N-ammonia or ^99m^Tc with another 20 minutes of scan time. For SPECT, scanning occus within 20 min. Qualitative and quantitative myocardial blood flow as well as cardiac function will be tabulated for comparison. The images will be reviewed by two consensus readers.

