**Study Design:**

This study is designed as a single-centre trial to determine diagnostic value of VCT for differentiating cardiac from non-cardiac causes of acute chest pain in ED. Approximately 150 patients will be enrolled over a period of approximately 15 months.

The patient enrolment and study procedures are illustrated in the study flow charter, Figure 1.

Figure 1: Study Flow charter

Patients with acute chest pain presenting in ED

Initial Management by ED staff

- Clinical history
- ECG
- Chest X-ray
- IV line establishment and routine blood draw
- Medical therapy initiated

No or patient refuse

Standard care

No patient F/U

Eligible for enrollment?

Yes and patient consent

- Detailed history by research staff
- Additional blood for testing
- CT data available for clinical use when it is clinically needed
- The axial images and reconstructed image sets will be sent to core-lab for blinded evaluation

VCT scan

Two consensus readers review all clinical information and make diagnosis

- Routine care by primary physicians
- Additional imaging or lab tests
- Collection of medication, discharge diagnoses and cost information

Patient follow-up

**Study Imaging Tests:** Chest CT and cardiac CTA.

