**Secondary Efficacy Endpoint(s):**

- Accuracy of VCT findings for triage patients to 1) implement appropriate therapy, 2) discontinue unnecessary/potentially harmful treatments, 3) limit observation time and diagnostic testing in the ED setting for acute chest pain.
- Potential cost saving using VCT to determine the aetiology of acute chest pain when compared to the standard care by changing patient management strategy.

**Safety Variables:** The following safety data will be collected and evaluated through the CT procedure:

- Unexpected adverse events
- Serious adverse events

**Gold Standard/Standard of Truth/Truth Panel:** Routine clinical information, including but not limited to, medical history, laboratory tests, ECG tests, other image tests and non-cardiac CT findings. To arrive at an adjudicated diagnosis, two board certified cardiologists independently reviewed all available evidence including history and physical, chest radiograph, non-cardiac CT findings, ECG’s, stress tests, cardiac catheterization, clinical follow up, and pharmacologic trials. Patients were categorized as ACS in the adjudicated diagnosis if 1) plasma troponin I >0.4 mg/dL during the index hospitalization, 2) a nuclear stress test with a summed difference score > 3, 3) an echocardiographic stress test with new or worsening dyssynergy in at least 1 ventricular segment, or 4) coronary stenosis >70% on catheterization. Each reviewer generated a prioritized adjudicated diagnosis list for each patient after the 3 month follow up data were available. Discrepancies between the reviewer’s lists were resolved by consensus. The highest priority consensus diagnosis was considered the cause of the patient’s symptoms for data analysis.

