**Statistical Methods:** The primary outcome is the diagnostic performance of CT compared to the standard of care to diagnose acute coronary syndrome (ACS). The classification accuracy of coronary CT to an adjudicated diagnosis for ACS. The diagnostic measures (e.g., sensitivity, specificity) for the CT diagnostic test for “significant CAD” (>50% stenosis) will be determined using the adjudicated diagnosis for ACS as the correct diagnosis. A >70% CTA stenosis will also be tested as a binary variable. Empiric confidence intervals will be calculated for each point estimate. Receiver operator classification (ROC) curves and area under the curve (AUC), both binary and empiric, will also be calculated. Classification accuracy between ECG-gating techniques (i.e., P-CT and R-CT) will be compared by relative probability estimates.

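### One rest-stress schedule is set for both nuclear tracers, but its 30-minute wait for decay suits 13N-ammonia and not 99mTc-tetrofosmin

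*Protocol*

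**What the plan says.** The Radionuclide Stress Testing section of the protocol allows SPECT or PET when the care team asks for stress imaging. It then gives a single sequence:

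- **Rest:** 20 mCi of 99mTc-tetrofosmin or of 13N-ammonia, followed by a 10-minute acquisition.
- **Wait:** "After approximately 30 minutes for radiotracer decay, stress testing with IV dipyramidole or adenosine begins".
- **Stress:** "At approximately 6 minutes, a PET scan is acquired using 20 mCi of" either tracer, so both the PET tracer and 99mTc appear in a sentence about a PET scan.
- **SPECT only:** "For SPECT, scanning occus within 20 min". This concerns scan timing and changes neither the wait nor the activity.
- **Reading:** "The images will be reviewed by two consensus readers", and the perfusion and function results are tabulated.

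The Gold Standard paragraph lists "a nuclear stress test with a summed difference score > 3" as one of four alternative criteria for ACS. Under Statistical Methods, CT sensitivity and specificity "will be determined using the adjudicated diagnosis for ACS as the correct diagnosis".

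**The concern.** The stated purpose of the wait is decay of the rest tracer. That makes sense for a tracer with a half-life of minutes. For one with a half-life of hours, almost all the rest activity is still present when the second, equal activity is injected, so the stress image is partly a second copy of the rest image. A segment that is normal at rest and under-perfused at stress is then partly filled in. The summed difference score measures the change between the two images, so for reversible defects this contamination can leave it unchanged or lower it, but does not raise it.

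At stake is the meaning of the cut-off of 3 in the reference standard. A SPECT patient near the cut-off, with no other qualifying criterion, could fail to meet the nuclear criterion where the same patient studied with 13N would meet it. If that patient were then adjudicated as not having ACS, a positive CT would count as a false positive instead of a true positive, and a negative CT as a true negative instead of a false negative.

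**Working it through.** **Inputs from the protocol (Radionuclide Stress Testing):** equal activities of 20 mCi; rest scan 10 min; wait about 30 min; stress acquisition at about 6 min.

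**Assumptions not in the protocol:** half-life T of 9.97 min for 13N and 361 min for 99mTc; stress-to-rest uptake ratio u from 1 to 2; no rest subtraction; tracer retained in the myocardium unless stated. The gap t between injections is 30 min if the wait runs from the rest injection, or 10 + 30 + 6 = 46 min if it follows the scan and the stress tracer is given 6 min into stress.

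**Step 1. Fraction of rest activity left, r = 2^(-t/T)**

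| Tracer | t = 30 min | t = 46 min |
|---|---|---|
| 13N | 0.124 | 0.041 |
| 99mTc | 0.944 | 0.915 |

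Varying T over 9.9-10.0 min and 350-370 min moves the 30-minute values only to 12.2-12.5% and 94.2-94.5%. The wait removes most of the 13N, though not all of it, and hardly any of the 99mTc.

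**Step 2. Rest share of the stress image at equal activities, r/(u + r)**

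- 99mTc: from 0.944/(1 + 0.944) = 0.486 to 0.915/(2 + 0.915) = 0.314, so 31-49%.
- 13N: from 0.124/1.124 = 0.110 to 0.041/2.041 = 0.020, so 2-11%.
- 99mTc if 20% of the rest tracer also washes out (0.8r in place of r): from 0.755/1.755 = 0.430 to 0.732/2.732 = 0.268, so 27-43%.

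**Step 3. Effect on a reversible defect.** Take a segment that is normal at rest and has 50% of normal uptake at stress. Its displayed uptake is (0.5u + r)/(u + r).

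- 99mTc: 1.444/1.944 = 0.743 (u = 1, 30 min) to 1.915/2.915 = 0.657 (u = 2, 46 min), so the segment shows as 66-74% of normal.
- 13N: 0.624/1.124 = 0.555 to 1.041/2.041 = 0.510, so 51-56%.

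**Step 4. Wait that 99mTc would need** to fall to the fraction 13N reaches: 361 × log2(1/0.124) = about 18 h, or 361 × log2(1/0.041) = about 28 h.

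**Step 5. A same-day 1:3 split of rest to stress activity**, for comparison. Replace r by r/3: 0.315/(1 + 0.315) = 0.239 to 0.305/(2 + 0.305) = 0.132. The rest share falls to about 13-24% but does not vanish.

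**The case against.** The strongest reply is that this is a clinical test and not a study procedure. The care team orders it, the protocol's own list of study imaging tests names only chest CT and cardiac CTA, and nuclear imaging falls under "Additional imaging or lab tests" in the Study Design flow chart. The section also reads like a PET description into which SPECT was merged. A PET scan with 99mTc cannot be done as written, so a competent laboratory would follow its own routine. This stands as a reason to expect less harm in practice and to keep the severity low. It does not make the text right: the protocol states the activities and the wait, gives a reason for the wait that fails for one of the two tracers, and has the images read and tabulated for the study.

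A second reply is that the nuclear score is only one of four criteria and that adjudication draws on much more: "Each reviewer generated a prioritized adjudicated diagnosis list for each patient after the 3 month follow up data were available". This also stands, and the adjudicators may well correct a misleading score. But this section does not call for the activities given or the injection times to be recorded, so they may not know which studies were affected.

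A reader might go further and multiply scores by the contrast retained, to conclude that a particular true score drops below 3, that only displayed scores just under the cut-off are in doubt, or that a 1:3 split keeps a true 4 above 3. The protocol does not support this. It does not say how the score is built, and such scores are normally sums of integer segment grades. With a retained contrast u/(u + r) of 0.51-0.69, four segments graded 1 could each still round to 1 and leave the total at 4, or each be read as 0 and bring it to 0. The direction of the bias is clear; the shift in any given score is not.

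**Conclusion.** The point holds as a minor error in the protocol text. One schedule is applied to two tracers, and its wait does what it is said to do for only one of them. With the half-lives assumed above, 92-94% of the 99mTc remains at the stress injection against 4-12% of the 13N. At equal activities, an uptake ratio of 1 to 2 and no subtraction, rest counts form about 31-49% of the 99mTc stress image against 2-11% for 13N. If the schedule is followed as written, reversible defects on SPECT can be partly masked and the summed difference score biased downward.

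A reader might infer that the reference standard is therefore materially biased and that the CT sensitivity and specificity are wrong. The document does not support that. It gives neither the number of SPECT studies, nor the laboratory's actual practice, nor the distribution of scores, and the other criteria and the follow-up may lead to the same diagnosis. The number of patients affected and the effect on CT accuracy cannot be derived.

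**What to change.** In Radionuclide Stress Testing:

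- Limit the 30-minute wait and the equal activities to 13N-ammonia PET, and remove 99mTc from the PET sentence.
- Give 99mTc SPECT its own schedule: a same-day split with low rest and high stress activity, separate days, or decay-corrected rest subtraction. If the laboratory already works differently, describe that routine instead.
- Record five items for each nuclear test: tracer, both activities and both injection times.

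In the Gold Standard paragraph, leave the cut-off of 3 unchanged and do not reclassify SPECT scores. Tell the adjudicators of any uncorrected, equal-activity, same-day SPECT study, whatever its displayed score.

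The cost is a reworded section, five data fields and no extra patients. Each SPECT option has a price. Halving the rest activity (for example 10 mCi at rest and 30 mCi at stress, the same 40 mCi total as 20 + 20) raises relative noise in the rest scan by √2, about 1.4 times, or needs 20 minutes instead of 10 for the same counts. A 1:3 split still leaves about 13-24% rest counts. Subtraction adds noise, and separate days take longer.

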**Coronary Angiography Image Analysis:**

If invasive coronary angiography is performed on a clinical basis, the digital coronary angiograms will be surveyed independently by two expert readers blinded to the patient history and coronary stenoses deemed >30% are evaluated by quantitative coronary angiography (QCA). At least 2 orthogonal diastolic views are used for each lesion. Automated vessel border detection is performed (ADAC/Philips, Bothell, WA) and luminal diameter both proximally and distally as well as within the lesion is measured; percent diameter stenosis is then calculated. The region of the myocardium supplied by the artery is estimated from the distribution of the vessel and its branches onto a polar map plot.

**Cost Analysis:**

After hospitalization, the total cost will be estimated by total charges as established through the hospital billing office and physicias billing office. These costs will be compiled and compared to the current charge for a thoracic CT scan. A fictive cost will then be determined base on diagnosis and treatment using the CT results and that will be compared to the actual cost incurred by the patient without the CT results . The risk/benefit ratio will be compiled using the risk of complications due to the CT scan (such as renal insufficiency) to the diagnostic benefits of the scan.

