Recent rapid advancement of multislice CT technology has allowed faster scanning times, better image resolution, and less intravenous contrast for visualization of structures. CT angiography holds the promise of enabling a non-invasive evaluation of the small coronary arteries that supply the heart. Four, 8, and 16 slice CT scanners have been used to imaging coronary arteries but poor spatial resolution and blooming artefact off calcified atherosclerosis has resulted in a significant number of coronary segments (up to 35% with 16 slice) that could not be evaluated using these scanners.

General Electric Healthcare has developed an innovative LightSpeed VCT. With the VCT scanner, 64-channels worth of data can be acquired in a single rotation, which allows cardiac CT data acquisition to be accomplished in the range of 5 seconds or 5 heart beats.

The newer, faster CT machine allows evaluation of coronary anatomy as well as atherosclerotic blockages with image resolution that approximates that of invasive coronary catheterization, the current gold standard test for coronary artery disease. **T**he 64 slice CT as an evaluation tool for patients presenting at ED with acute chest pain but with low to intermediate risk for angina would potentially allow rapid triage patients to 1) implement appropriate treatments, 2) ensure discontinuation of potentially harmful treatments, and 3) limit observation time and diagnostic testing in the acute setting.

In the ACUTE CT study, we propose using VCT as a first line imaging modality to evaluate patients presenting with acute chest pain in ED.

The hypothesis of the study is that

1. in low to intermediate CAD risk patients presenting with acute chest pain in ED, VCT examination will be able to exclude obstructive CAD as a cause for cardiac chest pain compared to routine evaluation and to accurately diagnose non-cardiac causes of acute chest pain by detecting presence of pulmonary embolus, aortic dissection, or other causes of chest pain.
2. the findings of VCT examination are able to accurately triage patients for proper management strategy
3. VCT examination will be able to reduce cost of and time required for managing patients with acute chest pain.

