**Secondary Objectives:**

- To evaluate impact of the VCT findings on patient management.
- To evaluate the cost of VCT for determining the aetiology of acute chest pain when compared to the standard care.

**Number of Subjects Planned:** 150

**Inclusion Criteria:** Subjects may be included in the study if they meet all of the following criteria:

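### Cost is measured by unconverted billed charges but reported as cost saving; the size and possibly the sign of the saving depend on cost-to-charge ratios that the protocol does not address

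*Protocol*

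**What the plan says.** Three places in the protocol set a question about cost. The third hypothesis, at the end of the Rationale, is that "VCT examination will be able to reduce cost of and time required for managing patients with acute chest pain". A secondary objective is "To evaluate the cost of VCT for determining the aetiology of acute chest pain when compared to the standard care". The matching item under Secondary Efficacy Endpoint(s) is "Potential cost saving using VCT to determine the aetiology of acute chest pain when compared to the standard care by changing patient management strategy".

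The Cost Analysis section sets the measure: "the total cost will be estimated by total charges as established through the hospital billing office", together with the physicians' billing office. It continues: "These costs will be compiled and compared to the current charge for a thoracic CT scan". A fictive cost is then built from the diagnosis and treatment that the CT results would have led to, and "that will be compared to the actual cost incurred by the patient without the CT results".

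The section gives no cost-to-charge ratio, no statement of whose cost is meant (hospital, payer or patient) and no amount for any item.

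**The concern.** Within one short section the quantity is called charges, then costs, then actual cost, as if these were the same. A charge is what is billed. What the hospital spends, or what a payer or patient pays, can differ from it, and the gap need not be the same for every department.

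Putting charges on both sides does not remove the problem. The Rationale describes usual care as 6 to 24 hours of observation with repeated enzyme tests, followed by stress testing or catheterization. CT is expected to shorten observation and reduce testing. The comparison therefore adds an imaging charge and takes away bed, laboratory and other test charges. If the ratio of cost to charge differs between these, the difference in charges is not a rescaled difference in cost.

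At stake is what the trial may conclude on its third hypothesis: a difference in bills could be published as a cost saving.

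**Working it through.** The protocol states no charge, cost, ratio or saving, and ties no power calculation to this endpoint, so there is no figure of its own to reproduce. The check asks how far a saving on charges can differ from a saving in cost. **All inputs below are assumptions.**

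**Set-up.** B = bed and observation charge, T = charge for other tests, C = CT charge, s = share of usual care still used after CT. r_B, r_T and r_C are the ratios of cost to charge.

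- Saving on charges = (B + T) − [C + s(B + T)]
- Saving in cost = (B·r_B + T·r_T) − [C·r_C + s(B·r_B + T·r_T)]

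**Uniform ratio r.** The saving in cost is r times the saving on charges, so the absolute saving is inflated by 1/r: 1/0.25 = 4.0, 1/0.4 = 2.5, 1/0.6 = 1.7. Numerator and denominator both shrink by r, so the percentage saving does not change.

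**Unequal ratios.** Take B = 60, T = 40, s = 0.4. With C = 30 the saving on charges is 100 − (30 + 40) = 30 units, or 30%. With C = 50 it is 100 − (50 + 40) = 10 units, or 10%.

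| C | r_C | r_B | r_T | Usual care, cost | CT pathway, cost | Saving in cost |
|---|---|---|---|---|---|---|
| 30 | 0.5 | 0.5 | 0.5 | 50 | 15 + 20 = 35 | 15 (30%) |
| 30 | 0.2 | 0.6 | 0.2 | 36 + 8 = 44 | 6 + 17.6 = 23.6 | 20.4 (46%) |
| 30 | 0.2 | 0.6 | 0.6 | 60 | 6 + 24 = 30 | 30 (50%) |
| 30 | 0.6 | 0.2 | 0.2 | 20 | 18 + 8 = 26 | −6 (−30%) |
| 50 | 0.2 | 0.6 | 0.2 | 44 | 10 + 17.6 = 27.6 | 16.4 (37%) |
| 50 | 0.6 | 0.2 | 0.2 | 20 | 30 + 8 = 38 | −18 (−90%) |

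**What drives the direction.** Let r̄ = (B·r_B + T·r_T)/(B + T). Subtracting the two percentages gives

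percentage on charges − percentage in cost = [C/(B + T)] × (r_C/r̄ − 1).

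Charges overstate the percentage saving when CT has a higher cost-to-charge ratio than the care it replaces, and understate it when CT has a lower one. The saving in cost stays positive only while r_C/r̄ < (1 − s)(B + T)/C, which is 60/10 = 6, 60/30 = 2 and 60/50 = 1.2 for C = 10, 30 and 50.

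**Grid.** Each ratio was set to 0.2, 0.3, 0.4, 0.5, 0.6, 0.8 or 1.0, giving 7³ = 343 combinations for each CT charge.

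| C | Absolute saving on charges too high | too low | Percentage too high | too low | Saving in cost no longer positive |
|---|---|---|---|---|---|
| 10 | 331 | 11 | 158 | 175 | 0 |
| 30 | 282 | 55 | 158 | 175 | 44 (39 negative, 5 exactly zero) |
| 50 | 199 | 141 | 158 | 175 | 125 (123 negative, 2 exactly zero) |

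These counts are not probabilities. They show only that the direction is not fixed, and that the sign is most at risk when the saving on charges is small.

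**The case against.** The strongest reply is that nothing is hidden. The section says openly that charges serve as the estimate, and it values the CT by its charge too, so both sides are on one basis. Under a uniform ratio the percentage saving is exactly right. The reference to cost incurred by the patient may point to a patient or payer viewpoint, for which the hospital's resource cost is not obviously the right target. This is a single-centre pilot, the endpoint is secondary and is called a potential saving, and a statistical analysis plan that is not shown could add a conversion. Every ratio used above is assumed.

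Much of this stands. The protocol does not show that mark-ups differ between departments at this hospital, only that the result depends on whether they do. It also does not call the charges list prices or show that nobody pays them, so neither claim should be made.

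The mismatch itself remains. The protocol positively fixes charges as the measure and words the result as cost. A declared proxy is still a proxy, and a common basis cancels only under equal ratios. If a patient or payer viewpoint is meant, the protocol should say so, and billed charges would still need to be shown to equal what is paid.

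**Conclusion.** The point holds as a mismatch between the measure and the claim. Unconverted hospital and physician charges cannot, without further information, support a statement about cost saving.

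A reader might go further and infer that the saving is overstated. The documents do not support that. It is true of the absolute saving under a uniform ratio below 1 (4.0 to 1.7 times for assumed ratios of 0.25 to 0.6), but the percentage is then unaffected. With unequal ratios the error runs either way: in the examples with C = 30, a saving on charges of 30 units became anything from a saving in cost of 30 units to a loss of 6, and with C = 50 a saving of 10 units became 16.4 or −18. Direction and size are unknown until ratios are available.

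These figures rest wholly on assumed charges, an assumed 40% of usual care retained, and assumed ratios. The diagnostic-performance primary outcome is untouched. Billing records can be converted or relabelled after collection, so nothing is lost beyond repair. The change is worth making because it decides what may be said about the third hypothesis.

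**What to change.** In the Cost Analysis section:

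1. State the perspective (hospital, payer or patient).
2. If it is the hospital's, collect itemised charges by billing department, multiply them by the hospital's department-level cost-to-charge ratios on both the actual and the fictive side, and make the converted difference the cost endpoint.
3. Value physician bills separately on a stated basis, because the hospital's ratios do not cover them.
4. Show unconverted charges as a secondary display, labelled as charges.
5. If ratios cannot be obtained, rename the endpoint as a difference in charges, make no claim of cost saving, and show how the result moves over a plausible range of ratios. Reword the secondary objective and the third hypothesis to match.

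The price is a request to the finance office, bills split by department, and a fictive side built item by item so that ratios can be applied to it. No further patients or procedures are needed. The reported saving may become larger or smaller.
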